**Reporting Adverse Events (AEs)**

PI [name] will meet regularly with all study investigators to review the details of data acquisition and analysis as well as any minor problems. AEs will be assessed for each subject at every in-person visit. In the event of any minor or significant AE, the PI will be contacted immediately. The PI will be responsible for the generation of summary reports documenting this process and outcomes which will be included in the Continuing Review reports to the IRB. Serious AEs (events that are unexpected, and related or possibly related to the research and that indicate there are new or increased risks to subjects) will be reported by telephone or email to the Partners IRB according to current PHRC Adverse Event Reporting Policy. All AEs (if not serious) will be reported in writing to the Partners Human Research Committee via Insight. All information regarding experimental subjects will be kept in a locked drawer in PI [name]’s locked office. All data will be identified by a unique code number.

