**Planned Safety Monitoring**

This study will be monitored by PI, [name], using a Data and Safety Monitoring Plan (DSMP). It is considered necessary for the purpose of monitoring the safety of the study that PI review not only AEs and SAEs, but other data that may reflect differences in safety between treatment groups. This includes treatment retention rates, reasons for drop-out, and clinical outcomes. The main purposes of the DSMP will be to (1) ensure the continued safety of study participants, (2) monitor enrollment and retention, (3) confirm that there are no issues with data confidentiality, and (4) determine whether there is an unacceptable level of risk and increase number of adverse events due to cannabis abstinence. The PI will have overall responsibility for safety and data monitoring on a day-to-day basis.

An independent Data and Safety Monitoring Board (DSMB) will be appointed for this study to assess safety of this clinical trial by determining whether there is an unacceptable level of risk due to cannabis abstinence and whether an increased number of adverse events occur in the CB-Abst group compared with the CB-Mon group. A DSMB will be created at the beginning of year 1, as an independent body charged with ensuring that the safety of study subjects is protected and that the scientific goals of the study are being met. The DSMB will consist of four members whose expertise spans fields such as (1) digital monitoring via smartphones, (2) longitudinal research with high-risk suicidal participants, (3) adolescents, and (4) biostatistics. Each member of the DSMB will not otherwise be associated with the trial and the study investigators will not be members of the DSMB. Safety data will be reviewed by the DSMB every 6 months after the recruitment period begins. The DSMB will receive summary reports on recruitment, retention and description of all adverse events and review them at each biannual DSMB meeting. Subject information provided to the board will be identified only with study IDs to protect the confidentiality of subjects.

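### Serious adverse events are defined by unexpectedness, relatedness and new risk, not by outcome, so a grave event judged expected or unrelated is classed as non-serious

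*Protocol*

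**What the plan says.** Under Reporting Adverse Events (AEs), the protocol explains serious AEs in a parenthesis: "events that are unexpected, and related or possibly related to the research and that indicate there are new or increased risks to subjects". Events in this class "will be reported by telephone or email to the Partners IRB according to current PHRC Adverse Event Reporting Policy". The rest take another path: "All AEs (if not serious) will be reported in writing to the Partners Human Research Committee via Insight". Whatever the class, "In the event of any minor or significant AE, the PI will be contacted immediately".

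Planned Safety Monitoring then uses the term SAE without defining it again, requiring that the "PI review not only AEs and SAEs, but other data that may reflect differences in safety between treatment groups". The same section sets up a DSMB that is to determine, among other things, "whether an increased number of adverse events occur in the CB-Abst group compared with the CB-Mon group". On what the board sees and when, it says: "Safety data will be reviewed by the DSMB every 6 months after the recruitment period begins" and "The DSMB will receive summary reports on recruitment, retention and description of all adverse events and review them at each biannual DSMB meeting".

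**The concern.** Seriousness is normally a property of what happened to the participant: death, danger to life, admission to hospital, lasting disability, or a medically important event such as a suicide attempt. Whether the event was foreseen, and whether the research may have caused it, are separate judgements made about an event already known to be serious or not. The protocol merges them. Its parenthesis is the usual test for an unanticipated problem, placed under the name of serious AEs.

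The population makes this more than a matter of terms. Participants are adolescents aged 12 to 18 with depressive symptoms, and suicidal ideation is a primary EMA outcome. Hypothesis 2.1 (Specific Aims and Objectives) predicts that negative mood and suicidal ideation will worsen in CB-Abst, and not in CB-Mon, in the first week of withdrawal. Someone who applies the parenthesis to a suicidal event in that week can point to the protocol's own hypothesis as grounds for calling it expected. The harm that the DSMB is asked to watch for is then among the easiest to place outside the serious class.

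**Working it through.** No arithmetic applies: the protocol gives no figure on this point and no event rate. The check is to read the definition as a rule, apply it, and look for anything elsewhere that overrides it.

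**The rule.** Three conditions are joined by the word and: (a) the event was unexpected; (b) it was at least possibly related to the research; (c) it points to a new or greater risk. All three must hold. None refers to outcome.

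**The rule applied.**

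| Event | Judgement | Condition failed | Class as written |
|---|---|---|---|
| Psychiatric admission in withdrawal week | Expected | (a) | Non-serious |
| Suicide attempt | Unrelated | (b) | Non-serious |
| Death | Unrelated | (b) | Non-serious |
| Suicide attempt | Unexpected and possibly related, but no new or greater risk seen | (c) | Non-serious |
| Mild event | Unexpected, possibly related, new risk seen | None | Serious |

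The last row shows that the rule also errs the other way: a mild event can qualify as serious.

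**Search for an overriding definition.** Planned Safety Monitoring names SAEs but does not define them. The suicide-risk steps under Risks and Discomforts deal with follow-up of EMA ratings, not with classifying AEs. Outcomes Monitoring deals with data quality and protocol deviations. Assessment Techniques provides for the C-SSRS at V2 to V12, which records suicidal behaviour but does not say how such behaviour is to be classed as an AE. None gives an outcome-based definition.

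**What changes for a misclassified event.**

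| Recipient | Classed serious | Classed non-serious |
|---|---|---|
| PI | Immediately | Immediately |
| IRB / Human Research Committee | Telephone or email | In writing, via Insight |
| DSMB | 6-monthly description of all AEs | The same |
| Label in PI review | SAE | AE |

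The difference lies in the second and fourth rows: the route to the IRB and the label. The section gives no time limit for either route, so it cannot be said from the text how much later the written report arrives.

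**The case against.** The strongest reply is that little depends on the label. The PI hears of every AE at once. Non-serious AEs still go to the committee. The DSMB's comparison of the arms is set on adverse events in general, not on serious ones, and the board receives a description of them all. Suicidal behaviour is captured by the C-SSRS at each visit from V2 to V12, and EMA ratings are checked twice daily, whatever an event is later called. The serious route also refers to an institutional reporting policy, and monitoring follows a Data and Safety Monitoring Plan. Neither is shown, and either might define seriousness by outcome.

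Most of this stands, and it limits the point. It does not repair the definition. If the policy or the monitoring plan holds an outcome-based definition, the protocol's parenthesis conflicts with it and still needs correcting.

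Three stronger readings are tempting, and the documents do not support them:

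- **That such events go unreported.** They do not; they are reported as non-serious.
- **That the DSMB's comparison of the arms is biased.** That comparison is on all AEs. A misclassified admission still counts in it, and no section assigns a by-arm comparison to a count of SAEs.
- **That relatedness is judged by staff who know the arm.** The protocol does not say who judges it or whether that person is blinded. It says only that the staff who administer the mood and suicidality questionnaires are blind.

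Nor is it certain that suicidal events would be called expected. Hypothesis 2.1 predicts a rise in ideation, not in attempts or admissions, and the protocol text gives no list of expected events. The rule leaves the matter open, and that is itself the weakness.

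**Conclusion.** The point holds as an error of definition. The protocol gives the name of serious AEs to a test for unanticipated problems, and nothing else in it defines seriousness by outcome. An event of grave outcome that fails any one of the three conditions loses the serious label and the telephone or email route to the IRB. It keeps its place in the reports to the PI, in the written reports to the committee and in the DSMB's 6-monthly review.

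The size cannot be stated as a number. It depends on how many such events occur and how often they are judged expected or unrelated, and the protocol gives neither. The conclusion assumes that staff apply the parenthesis as written and that the policy and monitoring plan, which are not shown, do not override it in practice. The planned tests of mood and suicidal ideation are untouched. The correction should be made because the error is plain, the population is at risk of the events concerned, and the change is cheap.

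**What to change.** Three changes to the sections on AE reporting and safety monitoring:

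1. Define a serious AE by outcome: death, a life-threatening event, hospitalisation, lasting disability, or another important medical event such as a suicide attempt. State that this applies whatever the expectedness or relatedness.
2. Keep the present three-part wording, but as the separate definition of an unanticipated problem. Check both definitions against the institutional policy that the section cites.
3. In the DSMB reports, show serious AEs by arm, with relatedness as a secondary column, so that the board sees the gravest events as a class without a prior judgement of cause.

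The cost is a wording amendment and one further table for the DSMB. No new data need be collected. The drawback is that a few more events enter the telephone or email route.

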**Planned Safety Monitoring**

This study will be monitored by PI, [name], using a Data and Safety Monitoring Plan (DSMP). It is considered necessary for the purpose of monitoring the safety of the study that PI review not only AEs and SAEs, but other data that may reflect differences in safety between treatment groups. This includes treatment retention rates, reasons for drop-out, and clinical outcomes. The main purposes of the DSMP will be to (1) ensure the continued safety of study participants, (2) monitor enrollment and retention, (3) confirm that there are no issues with data confidentiality, and (4) determine whether there is an unacceptable level of risk and increase number of adverse events due to cannabis abstinence. The PI will have overall responsibility for safety and data monitoring on a day-to-day basis.

An independent Data and Safety Monitoring Board (DSMB) will be appointed for this study to assess safety of this clinical trial by determining whether there is an unacceptable level of risk due to cannabis abstinence and whether an increased number of adverse events occur in the CB-Abst group compared with the CB-Mon group. A DSMB will be created at the beginning of year 1, as an independent body charged with ensuring that the safety of study subjects is protected and that the scientific goals of the study are being met. The DSMB will consist of four members whose expertise spans fields such as (1) digital monitoring via smartphones, (2) longitudinal research with high-risk suicidal participants, (3) adolescents, and (4) biostatistics. Each member of the DSMB will not otherwise be associated with the trial and the study investigators will not be members of the DSMB. Safety data will be reviewed by the DSMB every 6 months after the recruitment period begins. The DSMB will receive summary reports on recruitment, retention and description of all adverse events and review them at each biannual DSMB meeting. Subject information provided to the board will be identified only with study IDs to protect the confidentiality of subjects.

**Outcomes Monitoring**

Quality assurance procedures will include training of all study personnel (including psychology/psychiatry trainees) prior to initiation of the study and monitoring of subject enrollment and ensuring quality of data (source documentation and online in RedCap). Internal audits will be conducted under the supervision of the principal investigator, to assure that study data in RedCap are accurate and in agreement with source documentation, verify that consent for the study has been properly obtained and documented, and confirm that participants enrolled in the study meet inclusion and exclusion criteria. Any significant deviations from the protocol, including non-adherence to inclusion/exclusion criteria, errors in study procedures, or failure to complete assessments, will be reported to the Partners HRC as a protocol violation.

Participants will be terminated from this study if they fail to comply with study procedures, or if the opinion of the principal investigator, can no longer safely participate.

**Internal Monitoring (source data, protocol adherence, recordkeeping)**

The principal investigator and co-investigators will meet regularly with all study investigators to review the details of data acquisition and analysis as well as any minor problems. All study personnel will be trained on the collection of source data, protocol adherence, and recordkeeping as required by the MGB Research Institute. Primary research assistants will review source data, protocol adherence, and records daily and meet with the principal investigator and co-investigators weekly. The primary research assistants will also be responsible for the maintenance of training records for new study personnel.

1. **Privacy and Confidentiality**

Study procedures will be conducted in a private setting

Only data and/or specimens necessary for the conduct of the study will be collected

Data collected (paper and/or electronic) will be maintained in a secure location with appropriate protections such as password protection, encryption, physical security measures (locked files/areas)

Specimens collected will be maintained in a secure location with appropriate protections (e.g. locked storage spaces, laboratory areas)

Data and specimens will only be shared with individuals who are members of the IRB-approved research team or approved for sharing as described in this IRB protocol

Data and/or specimens requiring transportation from one location or electronic space to another will be transported only in a secure manner (e.g. encrypted files, password protection, using chain-of-custody procedures, etc.)

All electronic communication with participants will comply with Mass General Brigham secure communication policies

Identifiers will be coded or removed as soon as feasible and access to files linking identifiers with coded data or specimens will be limited to the minimal necessary members of the research team required to conduct the research

All staff are trained on and will follow the Mass General Brigham policies and procedures for maintaining appropriate confidentiality of research data and specimens

The PI will ensure that all staff implement and follow any Research Information Service Office (RISO) requirements for this research

Additional privacy and/or confidentiality protections

PI will ensure that all staff are trained on proper consent procedures to ensure participants and parents of minors are aware of situations where confidentiality needs to be broken to ensure safety.

